**The role of the manual**

The treatment manual will guide the selection of persuasive communication strategies as appropriate for each participant and will be based on underlying change mechanisms specified by the IMB theoretical framework. This has been developed with particular input from the research fellow (AP), current PEP health advisors, co-applicants CA, CL and collaborator BH (with input from all co-applicants). The manual addresses steps to eliciting information, scripts for likely scenarios and responses and techniques to bring the sessions to a close.

**Information provision and skills building**

Information about HIV risk behaviour, prevalence and strategies to minimise risk will be provided to those allocated into the intervention arm ('Ready for Action' Second Edition, and 'Get it on' condom guide both produced by the Terrence Higgins Trust). This will be either sent by post, email or accessed via the internet (as preferred) after baseline measures have been returned but before the intervention. The interventionist will prompt the participant to read the information if they have not already done so.

The skills building component of the intervention will be given during the telephone session in the form of interventionist provided information, and practical strategies needed to master these skills. An action plan will be developed and agreed on (between interventionist and participant) during the session and the participant will be asked to write this down and practice. The interventionist will also write down the agreed action plan and send this to the participant after the session (either by post, or email as indicated by participant). Questions about adherence to practicing the action plan will be included in the follow-up questionnaires.

**Vulnerable patients and disclosures**

If during the intervention the patient discloses current self-harming thoughts or behaviour towards themselves or another, they will be referred to their treating consultant, GP or psychiatric support provided by the GUM clinic (we will have a list of contacts for each referring centre). The breaking of confidentiality under these circumstances is detailed on the consent form.

### **Anonymity and confidentiality of data**

Participants anonymity will be protected by the allocation of a code (not a clinic or NHS number) for use on the database. Codes will be kept in a locked cupboard in the Department of Primary Care and Public Health, BSMS. Confidentiality of the data will be ensured by adhering to the Data Protection Act.

### **Confidentiality and data sharing between participant sites**

All patient related information to be shared through encrypted NHS email system.

### **Interventionist training and supervision**

The intervention will be delivered by a research fellow with experience of working with MSM populations in relation to sexual health and with experience of delivering motivational interviewing and educated to masters level. We have also costed in a 6 day advanced course in using MI with respect to sexual health run by Zest Consultancy (Members of the International Motivational Interviewing Network of Trainers), to refresh skills. CL is trained in motivational interviewing and will provide day to day supervision to the researcher. Additional supervision will be provided on a consultancy basis by a Consultant Clinical Psychologist (BH) who has extensive expertise of MI. The intervention based on the IMB Model will be developed with input from the steering group but particularly with expertise from CA and BH and piloted.

### **Treatment fidelity**

Assessing the fidelity of the treatment is an important component of successful research dissemination. Translating effective behavioural change interventions from this research setting to clinical practice can be facilitated better when treatment fidelity strategies are used as guidelines for implementing new interventions in the clinic.

In order to monitor the reliability and validity of the intervention, assessment of both the interventionist and the participant will be conducted as per National Institutes of Health (NIH) Behaviour Change Consortium 'best practice' recommendations. Ensuring same treatment dose within conditions will be ensured by a fixed number of sessions and by delivery within the intervention period (see intervention section). Ensuring interventionist skill acquisition and minimising 'drift' in interventionist skills will be minimised by the development and use of a treatment manual; by monitoring and providing feedback to the interventionist; and by providing adequate training. The gold standard method to ensure standard delivery of the intervention is to evaluate or code the sessions (through audiotape) according to predefined criteria. A validated instrument, the Motivational Interviewing Skill Code (MISC) [30], will be used to provide structured feedback, to monitor and document adherence to MI principles during weekly supervision. The interventionist will also be required to complete a process evaluation checklist (adapted from the NHS Health Trainer Handbook [31]) after each intervention session to remind them to include the appropriate skills and content for each intervention and minimise bias. The advisory board will be used to determine whether the treatment protocol has been adhered to during the recruitment and intervention period. Reduction of differences within treatments will be ensured by the use of one interventionist.

Should the valuation of the treatment delivery be found by BH to reduce, the researcher would undergo refresher training and mentoring with BH/CA.

## Measures

**Primary outcome:** The proportion of risky sexual practices.

Risk Behaviour outcome measure

A Risk Behaviour outcome measure has been developed to include items of potential HIV transmission-risk sexual behaviour: number of episodes of unprotected anal intercourse (UAI) (receptive and insertive) over a three month time period with individuals of unknown or HIV positive status, consistency of condom use, number of partners using no protection.

(Unprotected receptive oral sex with an HIV+ve person is associated with minimal HIV transmission risk and thus is not included).

**Secondary outcomes** (and method of assessment):

- i) Levels of adherence to PEP treatment (Morisky Medication Adherence Scale (MMAS) [32] adapted for use in PEP)
- ii) Number of subsequent courses of PEP (self-report and medical record review).
- iii) Levels of motivation to avoid risky sexual behaviours ('Measures of Motivation to Perform AIDS Preventive Behavior' questionnaire [33] adapted for use with MSM. This questionnaire provides assessment of attitudes, subjective norms and behavioural intentions in relation to HIV risk-reduction).
- iv) Levels of HIV risk-reduction information/ knowledge ('Health and Relationships Survey' [33] adapted for use with MSM. Items are summed to form an HIV prevention information scale score).
- v) Levels of risk reduction behavioural skills ('Behavioral Skills Measure' [33]. This consists of two subscales which assess the perceived difficulty of reducing HIV risk behaviour and the perceived effectiveness of methods to reduce risk).
- vi) Diagnosis of anal gonorrhoea
- vii) Diagnosis of HIV.

With the exception of adherence, all outcome measures will use a retrospective recall period of 'the past 3 months'.

Other factors assessed by self-report questionnaire at each time point will be alcohol and substance use. Socio-demographic (age, ethnicity, education, employment, relationship status) will be assessed at baseline. Experience of treatment side-effects will be assessed using a previously used measure at 3 month together with the measure of adherence.

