### **Objectives and hypotheses**

The primary aim is to examine the impact of motivational interviewing augmented with information and behavioural skills building (informed by the Information-Motivation-Behavioural Skills Model), over and above usual care, on risky sexual behaviour in MSM prescribed PEP after potential sexual exposure.

A secondary aim of this research is to examine the impact of the intervention on adherence to PEP.

Specifically we hypothesize that compared with treatment/ management as usual, those in the intervention arm will:

- 1) Report a reduction in the proportion of risky sexual practices (less unprotected anal intercourse (UAI) (receptive and insertive), increased use of condoms, a reduction in partners);
- 2) Have greater levels of adherence to PEP treatment;
- 3) Have lower rates of need (subsequent use) of PEP;
- 4) Have greater motivation to avoid risky sexual behaviours;
- 5) Have greater knowledge of risk reduction strategies;
- 6) Have greater risk reduction behavioural skills;
- 7) Have lower incidences of anal gonorrhoea;
- 8) Have lower incidences of HIV.

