### Baseline and follow-up assessments

Participants enrolled into the study will be asked to self-complete a questionnaire at four time points during the study (at 0,3,6,12 months). The baseline questionnaire will be administered at the recruitment stage, and upon receiving the consent forms and baseline assessments, participants will be randomly allocated to either intervention or control conditions (see randomisation section).

The second questionnaire will be posted to patients or accessed via email/the internet (as per consent) prior to their 3-month follow-up appointment with the clinic. Any patients who have not returned completed questionnaires before their '3-month' follow-up will be sent repeat copies (as per consent), and subsequently called on the telephone (if consented), and finally, may be approached by study staff at their clinic appointment.

The third questionnaire will be posted to patients or accessed via email/the internet (as per consent) 6 months after the end of PEP. Patients not returning their questionnaires will be sent repeat copies, and subsequently called on the telephone (as per consent). Those with a '6-month' follow-up appointment (depending on the recruitment site) and who have failed to return their questionnaire will be approached by study staff at their clinic appointment.

---

 Maximum of 2 repeat copies and 1 text/call/email if consented by patient.

The fourth questionnaire will be posted to patients or accessed via email/the internet (as per consent) 12 months after the end of PEP. Repeat copies, and subsequent telephone calls, will be used as reminders.

The recruitment period is for 12 months to allow sufficient numbers of participants to be recruited. A sample size of 250 (allowing for a 75% recruitment rate and 50% retention rate) is achievable within the time-frame and we anticipate that numbers will be higher given the increasing trends for PEP requests.

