## Frequency and duration of follow-up

The primary and secondary outcomes ii, iii, iv, and v will be collected at 3, 6 and 12 months after the end of treatment (and the end of the intervention). Secondary outcome i will be collected at 3 months only.

The follow-up period is for 12 months to determine intervention sustainability. Participants will be contacted by telephone prior to each follow-up assessment to remind them of their participation in the study and to ask their preference for follow-up assessment (postal, email/internet or via clinic attendance).

---

 Incidence data on rectal gonorrhoea will be collected as this is directly related to the risky sexual behaviour that we are assessing in this trial i.e. directly related to condom use.

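### The 3-month recall with forms at 3, 6 and 12 months leaves months 6 to 9 outside self-report, and the protocol does not say that other ascertainment of repeat PEP, gonorrhoea and HIV fills the gap

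*Protocol*

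**What the plan says.** The Measures section sets one recall rule for all outcomes and names a single exception: "With the exception of adherence, all outcome measures will use a retrospective recall period of 'the past 3 months". The same section lists repeat PEP as secondary outcome ii, with two sources: "Number of subsequent courses of PEP (self-report and medical record review". Anal gonorrhoea (vi) and HIV (vii) are listed only as diagnoses, the latter simply as "Diagnosis of HIV", with no source named.

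The timetable is in two places. Baseline and follow-up assessments has participants "self-complete a questionnaire at four time points during the study (at 0,3,6,12 months". Frequency and duration of follow-up adds: "The primary and secondary outcomes ii, iii, iv, and v will be collected at 3, 6 and 12 months after the end of treatment". Outcomes vi and vii are absent from that sentence, although a footnote says "Incidence data on rectal gonorrhoea will be collected as this is directly related to the risky sexual behaviour". There is no 9-month form. On length, the protocol says: "The follow-up period is for 12 months to determine intervention sustainability".

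Objectives and hypotheses words the event outcomes as quantities over time. Hypothesis 3 is that the intervention arm will "Have lower rates of need (subsequent use) of PEP". Hypotheses 7 and 8 speak of lower incidences of anal gonorrhoea and of HIV.

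**The concern.** A fixed look-back suits a repeated snapshot. For unprotected anal intercourse, each form describes the preceding quarter, and the skipped quarter is simply not sampled. Repeat PEP courses and new diagnoses are different, because they are events to be accumulated. If the question reaches back only 3 months, a man who had a further course in month 7 correctly answers no at month 12.

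By its wording the rule reaches these events, since only adherence is exempted. Two things follow for the self-reported part of the count. It is incomplete over a period chosen to show whether the effect lasts. It also depends on which forms come back and when: a missing form widens the gap, and a late 3-month form followed by an on-time 6-month form makes two windows overlap, so one course could be reported twice. An analysis plan cannot later recover an event that no question asked about.

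**Working it through.** **Inputs from the protocol**
- Recall window: 3 months (Measures).
- Follow-up forms: 3, 6 and 12 months after the end of PEP (Baseline and follow-up assessments; Frequency and duration of follow-up).
- Follow-up: 12 months.
- 125 men per arm, and a 0.01 significance level for secondary outcomes (Analyses plan and power calculation).

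The protocol states no coverage figure, so there is none to reproduce.

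**Coverage.** A form at month t covers t - 3 to t.

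| Form | Window |
|---|---|
| 3 months | 0-3 |
| 6 months | 3-6 |
| 12 months | 9-12 |

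Covered: 3 + 3 + 3 = 9 of 12 months (75%). Uncovered: months 6-9, 3 of 12 (25%). If the 6-month form is missing, the windows are 0-3 and 9-12, which is 6 of 12 months (50%). If items asked about the time since the last form, the windows would be 3 + 3 + 6 = 12 of 12 months.

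**Precision, self-report alone, constant event rate.** Expected events fall to 0.75 of the total. The variance of a log rate ratio is 1/E1 + 1/E2, where E1 and E2 are the event counts in the two arms, so its standard error rises by 1/sqrt(0.75) = 1.155.

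**Illustration.** The event rates below are assumptions and are not in the protocol. Assume also a rate ratio of 0.5, 125 men per arm all followed for 12 months, Poisson counts, and nothing added by record review. Power at two-sided 0.01 is approximately Phi(ln 2 / SE - 2.576), with ln 2 = 0.693.

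| Assumed courses per man-year | Coverage | Events | SE | Power |
|---|---|---|---|---|
| 0.4 v 0.2 | 12 months | 50 v 25 | sqrt(1/50 + 1/25) = 0.245 | about 60% |
| 0.4 v 0.2 | 9 months | 37.5 v 18.75 | sqrt(1/37.5 + 1/18.75) = 0.283 | about 45% |
| 0.2 v 0.1 | 12 months | 25 v 12.5 | sqrt(1/25 + 1/12.5) = 0.346 | about 28% |
| 0.2 v 0.1 | 9 months | 18.75 v 9.375 | sqrt(1/18.75 + 1/9.375) = 0.400 | about 20% |

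**Which outcomes the gap reaches**
- *Repeat PEP:* the self-report part has the gap. The record review has no stated dates. Courses obtained outside the recruiting clinic may not be in its notes, and self-report is the natural way to find them.
- *Gonorrhoea:* affected if it is taken from the questionnaire. The protocol does not say.
- *HIV:* the same, but a diagnosis is permanent and one made in month 7 could still be known at month 12. The one routine HIV recall described under the control arm is 3 months after PEP ends, so it does not fall in the gap.

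**The case against.** A reader might infer that events in months 6-9 are never counted. The documents do not support that. Repeat PEP has a second source, and a record review involves no recall. A recall period describes what a respondent is asked to remember, and the protocol puts no separate date limit on the review. For gonorrhoea and HIV no source is given and neither outcome is in the collection schedule, so it is not established that they rest on a 3-month question at all.

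A reader might also infer a biased comparison. The windows are the same in both arms, so a rate per covered month, or a rate ratio, is not biased by dropping the same segment from each if the rate ratio is stable over time. Dependence on form return is largely a missing-data question that an analysis plan may handle. Double reporting needs a late form, an event in the overlap and no check against records, and its size is unknown. The power figures hold only if record review adds nothing and follow-up is complete, whereas the protocol itself allows for 50% retention.

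All of this stands and limits the point. It does not remove it. The recall rule is stated rather than left open, its only exemption is adherence, and nothing says that another source spans the 12 months.

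**Conclusion.** The point holds in a limited form. Under the stated rule and schedule, self-report omits months 6-9, which is 25% of follow-up, for outcomes that the hypotheses treat as rates or incidences. The consequence is mainly lost completeness and precision: 25% of events and a factor of 1.155 on the standard error, assuming a constant rate and self-report alone. The loss would be smaller to the extent that record review recovers events. It is larger where forms are missing.

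Severity is moderate. The primary behaviour outcome is not affected, and no secondary result is shown to be invalid. The falls in power (60% to 45%, and 28% to 20%) illustrate scale under assumed rates and are not estimates for this trial.

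**What to change.** In the Measures section:
1. Limit the 3-month recall to the behaviour measure.
2. Word any self-report items for outcomes ii, vi and vii as since your last questionnaire, or since a stated date, excluding the index PEP course. A stated date also deals with missed and late forms.
3. State that record review for outcome ii, and for vi and vii where site records are already being read, runs over one fixed period ending 12 months after the end of PEP, for every randomised man whether or not his forms are returned. State the start date too, because randomisation follows consent and baseline while follow-up is timed from the end of PEP.

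The cost is a revised sentence, some reworded items and somewhat more record extraction, since record review is at present named only for outcome ii. The downside is that 6-month recall at the last form is less sharp than 3-month recall, which record review partly offsets.

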### **Trial treatment arms**

#### **Control group: Treatment/management as usual**

Both of the groups will receive 'treatment/management as usual': Patients are initially seen by a HA/SpN for an initial consultation, 5 day prescription of PEP and blood tests (for HIV, Hepatitis B and liver function). Patients receive their first follow-up appointment 5 days later to receive further PEP (if HIV-ve). After the 28 day treatment regimen patients receive either a face-to-face or telephone appointment with the HA/SpN to discuss their sexual health, adherence to PEP and the blood test results. At 4 months after exposure (3 months after the end of PEP) patients are recalled by the HA for HIV testing. In order to assess the impact of the intervention on outcome measures and IMB constructs, those allocated to control group 1 will be asked to complete all measures at 0,3,6, and 12 months.

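### Self-reported repeat PEP uses a three-month recall at months 3, 6 and 12, so months 6 to 9 fall in no window, and the record review that might fill the gap has no stated period

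*Protocol*

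**What the plan says.** The recall rule is in the protocol under Measures. It reads "all outcome measures will use a retrospective recall period of", and the period it then names is the preceding three months. Adherence is the only exception.

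The timetable is under Frequency and duration of follow-up. For repeat PEP and most other outcomes it says: "The primary and secondary outcomes ii, iii, iv, and v will be collected at 3, 6 and 12 months after the end of treatment". Adherence has its own line: "Secondary outcome i will be collected at 3 months only". Baseline and follow-up assessments confirms that participants "self-complete a questionnaire at four time points during the study (at 0,3,6,12 months", so there is no questionnaire at month 9.

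Repeat PEP is defined under Measures as "Number of subsequent courses of PEP (self-report and medical record review"). The matching hypothesis is "Have lower rates of need (subsequent use) of PEP". Hypotheses 7 and 8 concern the incidence of anal gonorrhoea and of HIV.

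The secondary outcomes are listed with a method of assessment for items i to v. Items vi (anal gonorrhoea) and vii (HIV) have none, and neither appears in the timetable. A footnote says that gonorrhoea incidence data will be gathered, without naming a source or time. Usual care includes an HIV test ("At 4 months after exposure (3 months after the end of PEP) patients are recalled by the HA for HIV testing"), but the protocol does not name that test as the source of outcome vii.

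**The concern.** One recall rule serves two kinds of outcome. For sexual behaviour, a three-month snapshot at each time point is sensible: the analysis compares levels of behaviour at those points, and nothing requires the windows to join up. A count of PEP courses, or an incidence, accumulates over time, and there a gap between windows removes events. A man who took a further course in month 7 would truthfully report none at month 12.

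The gap lies in the second half of follow-up, while the protocol gives sustainability as its reason for following men for 12 months. An analysis plan cannot later recover answers to a question that was never asked, so this is a matter of collection design.

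**Working it through.** The plan gives no figure of its own on this point to reproduce.

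**Inputs.** Recall window w = 3 months (Measures). Collection times t = 3, 6 and 12 months after the end of treatment, and follow-up of 12 months (Frequency and duration of follow-up).

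**Coverage.** Each questionnaire covers the interval from t − w to t:

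- t = 3: months 0–3
- t = 6: months 3–6
- t = 12: months 9–12

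Together these cover 3 + 3 + 3 = 9 of 12 months, or 75%. Months 6–9 are in no window: 3/12 = 25%.

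**Events lost, worst case.** Assume a constant event rate, self-report as the only source, and every questionnaire returned. The share missed is then 25%. The protocol gives no event rate, so the following rates are assumptions, applied to 250 men followed for 12 months:

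| Assumed events per person-year | Expected events | Inside a window (×0.75) |
|---|---|---|
| 0.05 | 12.5 | 9.4 |
| 0.10 | 25.0 | 18.8 |
| 0.20 | 50.0 | 37.5 |

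**Precision.** The standard error of a log rate ratio is about √(1/e₁ + 1/e₂), where e₁ and e₂ are the event counts in the two arms. Multiplying both counts by 0.75 multiplies the standard error by 1/√0.75 = 1.155, a rise of about 15%.

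**Effect of the record review.** Let r be the share of month 6–9 courses that the review recovers. The share missed becomes 0.25 × (1 − r), and the standard error factor becomes 1/√(1 − missed share):

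- r = 0: 25% missed, factor 1.155
- r = 0.5: 12.5% missed, factor 1/√0.875 = 1.069
- r = 1: none missed, factor 1

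The protocol does not fix r, because it does not state the period of the review.

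**After the change.** If the month-12 question reached back to the month-6 questionnaire, the windows would be 0–3, 3–6 and 6–12. That is 12 of 12 months.

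**The case against.** The strongest reply is that repeat PEP has a second source. Clinic notes can show a course in months 6–9 whatever the questionnaire asks, so 25% and 15% are ceilings. That stands. What remains is that the period of the review is not given and that the three-month rule is worded to cover every outcome except adherence.

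It can also be said that the windows are the same in both arms, so the gap costs precision and coverage and does not by itself bias the comparison within the observed months. That stands too. Nor do hypotheses 3, 7 and 8 name a time horizon; that they concern the whole follow-up is a reading, though a natural one for rates and incidences in a 12-month study.

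Four stronger readings are tempting, and the protocol does not support them:

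- **That gonorrhoea and HIV are asked about by questionnaire at 3, 6 and 12 months.** No section says so. They are listed as diagnoses, with no source. The gap reaches them only if the three-month rule is applied literally.
- **That notes review is confined to repeat PEP.** The section on duration and content of the intervention also names it for adherence. It is not named for the two diagnoses.
- **That courses begun in A&E would escape the notes.** Recruitment procedure says that the A&E and GUM routes merge at GUM PEP clinics within five days.
- **That arms may differ in testing and so in diagnoses.** This is a separate question from recall. No section says that the intervention changes testing, and the summary of usual care does not establish that rectal testing is absent.

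**Conclusion.** The concern holds for self-reported repeat PEP: the stated recall rule and timetable together leave months 6–9 unobserved, 3 of 12 months. The 25% loss of events and the 15% rise in standard error are upper limits. They rest on a constant event rate and on self-report being the only source, and they shrink to nothing if the notes recover every course in the gap.

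For anal gonorrhoea and HIV the point is narrower. The missing time and source are, on their own, unfilled detail. They matter here because the only collection rule that the protocol does state, read literally, would cut three months out of incidence data. An HIV diagnosis in the gap would still show in a later test or record, so HIV is the least affected.

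Only secondary outcomes are involved. The primary outcome, as a behaviour snapshot, is not harmed by the window. The change is worth making because it is cheap and cannot be made after the data are collected.

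**What to change.** 1. Under Measures, keep the three-month recall for sexual behaviour and limit the rule to it and to any other measure that is meant as a snapshot.
2. For repeat PEP, and for gonorrhoea and HIV if they are self-reported, ask about events *since your last questionnaire*, or *since the end of PEP* if one was missed.
3. State that the notes review for outcomes ii, vi and vii covers the full 12 months after PEP, so that the three-month rule plainly does not apply to it.
4. Add outcomes vi and vii to Frequency and duration of follow-up, and give their source under Measures.

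The cost is a changed stem for up to three questions and a few more fields in a notes review that is already planned. The questionnaires are due to be piloted and refined in any case. The drawback is a recall of six months at month 12, longer if a questionnaire was missed, but for events that men are likely to remember.
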